##### Digital patient record

In both parts of the main study, before T0, the medical/dental assistant will ask the patients whether or not they use a digital patient record or if they wish to activate this feature. If they use one and the participant agrees, diagnoses and risk scores will be deposited in the digital patient record in addition to the regular patient record. If patients wish to activate their digital record, T0 will take place as planned and the respective data will be deposited in the digital record retrospectively after activation. If patients do not wish to use the digital record or it cannot be used for technical reasons, data will be stored in the regular patient record only.

##### Baseline survey (T0)

Patients in both studies receive a written questionnaire on sociodemographic data and a self-disclosure of medical conditions. The questionnaire further contains a question on current, subjective health, translated from the publicly available, validated Short Form 36 (SF-36)-questionnaire by RAND Corporation [23]. Additionally, the questionnaire contains the respective questions for periodontitis/T2DM risk assessment (in the dentist study, this is only the case for the intervention group), so patients may calculate their risk score. The medical/dental assistant will be available for questions during this process. The further course differs depending on the study and risk-score.

###### T0 in general practices

Figure 2 provides an overview over T0 in general practices after patients receive the questionnaire described above.

**Fig. 2 Fig2:**
[figure not shown]
Baseline survey T0 in general practices

After T0, all patients receive usual care. During the following, regular DMP appointments, the GP will approach high-risk patients regarding the dentist appointment and potential measures that the dentist took. The follow-up survey T1 will take place 12 months after recruitment.

###### T0 in dental practices

Similar to the general practice study, the study pathways differ depending on the risk score of each patient. Additionally, the pathways differ between intervention and control group, as it can be seen in Fig. 3:

**Fig. 3 Fig3:**
[figure not shown]
Baseline survey T0 in dental practices

After T0, all patients receive usual care. During the following, regular dentist appointments, the dentist will approach high-risk patients in the intervention group regarding the GP appointment and potential measures that the GP took. The follow-up survey T1 will take place 12 months after recruitment.

##### Survey T1 (first follow-up)

The medical assistant in the general practice identifies all participating patients during a regular DMP-appointment. In the dental practice, the dental assistant identifies all participating patients during a regular appointment. Patients are asked to fill out another written questionnaire on their health and a potential periodontitis/T2DM diagnosis and therapy. Subjective health is once again assessed using the first question of the SF-36. To allow for a comparison with the patient’s subjective health at T0, question 2 of the SF-36 will be asked as well.

In the GP-study, the GP asks the patients about their potential periodontitis diagnosis and/or therapy. The primary endpoint measured during the regular DMP-appointment as well as the questionnaire data (including secondary endpoints) for T1 will be transferred to the research database by the medical assistant.

In the dentist study, the dentist in both control and intervention group asks the patients about their potential T2DM diagnosis and/or therapy. The current periodontal status and the periodontal services provided will, together with the questionnaire data, be transferred to the research database by the dental assistant.

The second, and final, follow-up survey takes place 6 to 12 months after T1, depending on when the patient was recruited for T0.

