##### In dental practices

New T2DM diagnoses among periodontitis patients who had not been diagnosed with a diabetes condition before. Recorded by dental assistants at T1 (after 12 months). [primary data]

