###### Dentist study

Sample size calculation refers to the primary endpoint and is therefore based on a Z-Test with non-pooled variance. We assume that, compared to the control group, the rate of new diabetes diagnoses will be 0.1 in the intervention group during the next 4 quarters [22]. For the control group we assume a rate of 0.05 (calculated from an internal analysis of insurer-data for the areas the study will be performed in). It is therefore assumed that the intervention allows for an additional 5% of diabetes diagnoses. Sample size is calculated with α = 5% and power = 80%. Patients are clustered in practices, so an intra-class-correlation of 0.03 and a cluster size of 8 patients per practice is assumed. Assuming an allocation ratio of 1:1 for control vs. intervention group, this results in a sample size of 528 patients (66 practices, 8 patients each) per group. With an assumed drop-out rate of 20%, sample size in each group will be 664 patients (83 practices, 8 patients each), adding up to a total of 1328 patients in 166 practices. Sample size calculation was performed using PASS v16.0.3.

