#### Dentist study

For the primary outcome, we will test the null hypothesis H_0_^ZA^: π_IG_^T1−T0^ = π_KG_^T1−T0^ against the alternative hypothesis H_1_^ZA^: π_IG_^T1−T0^ ≠ π_KG_^T1−T0^ on a two-sided significance-level of 5%. π_IG_^T1−T0^ and π_KG_^T1−T0^ represent the rate of new diabetes diagnoses between baseline (T0) and after 12 months (T1) in both groups.

Primary analysis will be performed using a generalized, logistic mixed model adequately representing the multi-level structure of data (practice on level 1, patients on level 2). For the test of H_0_^ZA,^ the „rate of new diabetes diagnoses between T0 and T1” will be used as the dependent variable. The model contains the practice as a random effect and the group (intervention vs. control), age, sex, insurance status, state and residential area as fixed effects on the patient level.

It can be assumed that claims data will be complete and missing values will only occur in the additional study data and the questionnaires. Missing values of the primary outcome will be imputed using multiple imputation [27] while accounting for the baseline-variables age, sex, insurance status and residential area. To check for the sensitivity of results, assumptions on missing values will be analyzed and an alternative procedure to handle missing data, such as an analysis of the full dataset, will be looked into. Further sensitivity analyses include sub-group analyses for both states and for insurance status.

Secondary endpoints will be presented descriptively first. Where appropriate, secondary endpoints will be explored similar to the primary analysis. For binary endpoints, logistic regression analyses will be performed. For continuous endpoints, linear regression analyses will be performed. For all estimated effects we will present descriptive p-values and 95% confidence intervals. All analyses are performed using a validated R environment with R version 4.0.0 or higher. The primary analysis is independently counter-programmed in SAS version 9.4 or higher.

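### The 12-month dental primary outcome is a questionnaire answer but is collected only at a regular dental visit, so missing outcomes can be related to exposure; this can bias the risk difference in either direction

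*Protocol article*

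**What the plan says.** All references are to the protocol article.

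- **Endpoint.** Under Primary endpoints, the dental endpoint is new diabetes diagnoses in periodontitis patients without a previous diabetes diagnosis: "Recorded by dental assistants at T1 (after 12 months). [primary data". No claims-data source is given for it.
- **Route.** Survey T1 states: "In the dental practice, the dental assistant identifies all participating patients during a regular appointment". Patients then complete a written questionnaire, and "the dentist in both control and intervention group asks the patients about their potential T2DM diagnosis and/or therapy". Survey T2 identifies patients in a similar way.
- **Intervention after baseline.** T0 in dental practices states: "During the following, regular dentist appointments, the dentist will approach high-risk patients in the intervention group regarding the GP appointment".
- **Intervention at baseline.** Baseline survey (T0) states that "the questionnaire contains the respective questions for periodontitis/T2DM risk assessment (in the dentist study, this is only the case for the intervention group".
- **Missing data.** The analysis population keeps drop-outs, following intention to treat. In the dentist-study analysis, missing primary outcomes are "imputed using multiple imputation [27] while accounting for the baseline-variables age, sex, insurance status and residential area". Assumptions about missing values are to be examined, and the only alternative named is a full-dataset analysis.
- **Leaving the practice.** Table 2 makes a permanent change of practice a patient termination criterion.

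**The concern.** The same event, a later dental visit, gives the trial its outcome and gives high-risk intervention patients part of their intervention. A patient who stops attending loses both, and the second loss occurs in one arm only. Non-attenders in the intervention arm may therefore be diagnosed at a different rate from attenders there.

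The intention-to-treat estimate needs the non-attenders' outcomes. The plan fills them in from attenders with the same age, sex, insurance status and residential area. This is sound only if, given those four variables, attenders and non-attenders have the same diagnosis rate. That assumption cannot be tested in the collected data, and the mechanism above gives a reason to doubt it.

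The reliance is largely avoidable, because a patient can report a diagnosis without sitting in a dental chair. HbA1c in the GP study is different, since it has to be measured. The dentist study is also the project's only randomised comparison.

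A lesser point concerns timing. T1 is set at 12 months and the hypothesis is a 12-month rate, but the information is taken at whichever regular appointment the patient keeps. The article does not say that only diagnoses made within 12 months count.

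**Working it through.** **1. The plan's own sample size** (inputs from Sample size calculation, Dentist study: rates 0.10 and 0.05, two-sided alpha 5% as in the hypothesis section, power 80%, unpooled Z-test, ICC 0.03, 8 patients per practice, drop-out 20%).

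- Per group before clustering: (1.960 + 0.842)² × (0.05 × 0.95 + 0.10 × 0.90) / 0.05² = 431.7
- Design effect: 1 + (8 - 1) × 0.03 = 1.21, giving 431.7 × 1.21 = 522.3
- Whole practices: 522.3 / 8 = 65.3, rounded up to 66; 66 × 8 = 528
- Drop-out: 66 / 0.8 = 82.5, rounded up to 83; 83 × 8 = 664

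Both stated figures, 528 and 664, reproduce. The drop-out allowance protects precision. It does nothing about bias from outcomes that are missing for a reason related to exposure.

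**2. Patients at issue.** 0.20 × 664 = 132.8 per arm, or 0.20 × 1,328 = 265.6 overall. This is all planned drop-out, of which non-attendance is only a part.

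**3. Illustration of the bias.** These assumptions are not in the article: attenders have the planning rates (10% and 5%), 20% are missing in each arm, control non-attenders have 5%, intervention non-attenders have a rate q between 5% and 10%, and the four baseline variables do not distinguish attenders from non-attenders.

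- True difference: (0.8 × 10% + 0.2 × q) - 5%
- Imputation by arm: each arm takes its own attenders' rate, giving 10% - 5% = 5.0 points
- Imputation without group: missing values in both arms take the pooled attender rate, (10% + 5%) / 2 = 7.5%. The intervention arm becomes 0.8 × 10% + 0.2 × 7.5% = 9.5%, the control arm 0.8 × 5% + 0.2 × 7.5% = 5.5%, a difference of 4.0 points

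| q | True difference | Bias, by arm | Bias, group omitted |
|---|---|---|---|
| 5% | 4.0 | +1.0 | 0 |
| 7.5% | 4.5 | +0.5 | -0.5 |
| 10% | 5.0 | 0 | -1.0 |

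(Percentage points.)

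**4. Sensitivity to those assumptions.**

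- Non-attender rates halved in both arms (5% and 2.5%): true difference 9.0% - 4.5% = 4.5 points. Bias is +0.5 by arm and -0.5 without group.
- Missing 10% in control and 30% in intervention, non-attenders at 5% in both: true difference (0.7 × 10% + 0.3 × 5%) - 5% = 3.5 points. By arm the estimate is 5.0 (bias +1.5). Without group the pooled rate is (0.7 × 10% + 0.9 × 5%) / 1.6 = 7.19% and the estimate is 9.16% - 5.22% = 3.94 (bias about +0.4).

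The table is therefore an illustration, not a set of bounds.

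**The case against.** A reader might infer that the plan inflates the intervention effect, by up to a quarter (5 points reported against 4 true). The article does not support that. It requires imputation by arm, and the printed list of imputation variables does not include group. On that list the same worst case gives exactly the true 4.0 points, and the other extreme understates by 1 point. It also requires control non-attenders to sit at the full control rate, which the article does not state.

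Other points stand in part:

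- **Exposure.** The intervention arm answers the risk questions at T0, so its non-attenders are under-exposed, not unexposed. What they miss is the dentist's follow-up, and only if they are high-risk. A rate of 5% for all of them is an extreme.
- **The 20%.** It is overall drop-out. Table 2 also lists withdrawal of consent, death, change of practice and loss of the practice, most of which a letter from the practice would not recover.
- **Procedural detail.** The article does not forbid rebooking or contacting non-attenders, and reminders and visit windows may be set out in the full protocol. T1 is also stated to fall 12 months after recruitment. However, a regular appointment is given as the route itself, not as one example of it.
- **Safeguards.** The practice receives 180 Euros per patient documented at T0, T1 and T2, diagnosis is asked about again at T2, and missing-data assumptions are to be examined. These help, but none secures the missing 12-month answer. T2 uses the same route and is intended for the secondary endpoints, and a full-dataset analysis, if it means complete cases, again rests on attenders.

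**Conclusion.** The point holds as a weakness in outcome collection. The article states a collection rule that loses a questionnaire-obtainable primary outcome for non-attenders, removes part of the intervention from some of the same patients, and leaves the gap to an imputation model whose listed variables carry no information on attendance. This can bias the risk difference, and neither size nor direction is fixed. Under the stated assumptions the bias is 0 to +1 point with imputation by arm and -1 to 0 points with group omitted, against a planned difference of 5 points. Unequal missingness can take it outside that range.

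No stated figure is wrong, and the sample size reproduces. The change is a cheap improvement that reduces dependence on an untestable assumption under either imputation model. It is not the correction of a demonstrated inflation.

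**What to change.** 1. In Survey T1, state that a still-consenting participant with no dental appointment in a fixed window around month 12 is sent the same T1 questionnaire by the practice, with one telephone reminder. Dental examination items stay missing.
2. Add a question on the quarter of diagnosis, and count only diagnoses within 12 months of T0 in the primary endpoint, whatever the date of collection.
3. Reconcile the change-of-practice termination criterion in Table 2 with the intention-to-treat population, so that questionnaire-only follow-up is allowed where consent continues. Without this, item 1 cannot reach patients who have moved to another dentist.

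**Cost.** Postage, one call by the assistant already named for the study, and one added question. If drop-out runs as planned, this concerns at most about 266 patients across both arms, and fewer in practice because not all drop-out is non-attendance. The mode of collection will differ for these patients and their periodontal data will be missing. Patients lost through withdrawal, death or practice closure are largely not recovered, so some reliance on imputation remains.

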##### Survey T2 (second follow-up)

The medical/dental assistants identify patients similar to T1. Patients in general practices are asked to fill out another written questionnaire on their health and a potential periodontitis diagnosis and therapy as well as the first two questions of the SF-36. These data and the current HbA1c-parameter will be transferred to the research database. T2 serves the purpose of checking on a permanent reduction of the HbA1c-parameter and to get a long-term picture of the secondary endpoints as well.

Patients in the dental practice are asked to fill out another written questionnaire on their health and a potential T2DM diagnosis and therapy as well as the first two questions of the SF-36. These data and the current periodontal status and the periodontal services provided will be transferred to the research database. T2 here serves the purpose of getting a long-term picture of the secondary endpoints.

##### Financial incentives and reimbursement for the provision of care

All participating practices receive a compensation of 250 Euros for participation. The medical/dental assistant responsible for the execution of the study within the practice receives 25 Euros for each patient recruited. Additionally, the practice receives 180 Euros for each recruited patient who is fully documented (survey and data transfer have taken place at T0, T1 and T2). Intervention patients receive the benefit of potentially learning about a present periodontitis/T2DM condition earlier than in usual care. They receive no monetary incentives.

Services in the intervention groups exceeding usual care (risk assessment, informing patients about their risk, doctor’s consultation, referral to the dentist/GP) are covered by the study budget and will be reimbursed with 30 Euros per patient. Practices are prohibited from billing these costs with the patient or health insurer.

### Process evaluation

The process evaluation is based on a written survey at two points in time and semi-structured interviews with care providers from both studies.

#### Written survey

All participating care providers in the intervention groups receive a written, pseudonymized questionnaire at the beginning and end of the observation period. Data will be stored and analyzed separately from the main study. The process evaluation is expected to cover 662 care providers from 331 intervention practices. With an assumed response rate of 60% there will be 397 completed questionnaires for each of the two measurement points. Topics will be acceptance of the implementation strategies (tutorials, financial aspects and billing, organizational support) as well as the implementation fidelity. Perceived barriers and enabling factors will be determined through a suitable framework, such as the CFIR-framework [24] or the TICD-framework [25] in a pre-post-comparison.

#### Interviews

A targeted sample of 40 care providers (equally divided into dental and general practices) will be invited to an additional phone interview during the intervention period. This sample size is usually sufficient to reach topical saturation and saturation of contents in the qualitative analysis. Interviews are planned to last 30–45 min and will be conducted using a semi-structured interview guideline that covers barriers and enablers of the implementation and criteria for maintaining the intervention as well as time expenditure for the study. Furthermore, factors influencing the motivation to participate in the study from the participants’ views will be explored. For the interviews there will be a separate form of informed consent. Interviews will be audio-recorded, transcribed verbatim and stored on a secure server. Transcripts will be pseudonymized.

### Economic evaluation

The economic evaluation focuses on costs and health benefits of the intervention compared to usual care. It uses trial data as well as claims- and DMP-data. Furthermore, there will be a discrete choice experiment (DCE) at the intersection of economic aspects and knowledge transfer regarding the implementation of new types of care (see Appendix 1 for details).

## Statistical analyses

### Analytic population

Primary statistical analysis is based on the full analysis set (FAS) following the intention-to-treat (ITT) principle and therefore being performed in accordance with current guidelines [26]. FAS includes all recruited patients (GP study) or those who were randomly assigned (dentist study) to a group, regardless of whether or not they actually participated in the intervention or dropped out of the study later on. This is the primary population for the evaluation of primary and secondary endpoints and study characteristics. To analyze the sensitivity of results, an analysis of the full dataset will be performed in addition. Drop-out and missing values will be accounted for by the intention-to-treat analyses. Missing values will be imputed.

### Statistical hypotheses and analyses

#### General practitioner study

For the primary outcome, we will test the null hypothesis H_0_^HA^: µ_IG_^T1−T0^ = µ_KG_^T1−T0^ against the alternative hypothesis H_1_^HA^: µ_IG_^T1−T0^ ≠ µ_KG_^T1−T0^ on a two-sided significance-level of 5%. µ_IG_^T1−T0^ and µ_KG_^T1−T0^ represent the reduction of the HbA1c-parameter between baseline (T0) and after 4 quarters (T1) in both groups.

Evaluation of the intervention contains descriptive and explorative statistical analyses of gathered study data as well as available claims data. The goal is an independent, scientifically valid and differentiated statement on effectiveness of the intervention regarding a reduction of the HbA1c parameter using an intervention study with parallel control group. The control group will be calculated from insurer claims data as well as DMP-documentation data across insurers. Using their registration number, intervention practices will be removed from the control group data. Study data will be described using descriptive methods.

Primary analysis will be a hierarchical, linear mixed model representing the multi-level structure of the data (level 1: practice, level 2: patient). For the test of H_0_^HA^, the dependent variable will be “reduction of HbA1c between T0 and T1”. The model contains the practice as a random effect and HbA1c at baseline (T0), age, sex, insurance status, state and residential area as fixed effects on the patient level. Here, only variables that are also included in claims data can be used.

It can be assumed that claims data will be complete and missing values will only occur in the additional study data and the questionnaires. Missing values of the primary outcome will be imputed using multiple imputation [27] while accounting for the baseline-variables age, sex, insurance status and residential area. Assumptions on missing values will be analyzed and an alternative procedure to handle missing data, such as an analysis of the full dataset, will be looked into.

Secondary endpoints will be evaluated descriptively and descriptive p-values will be presented with 95% confidence intervals for the corresponding effects. Where appropriate, secondary endpoints will be explored similar to the primary analysis. For binary endpoints, logistic regression analyses will be performed. For continuous endpoints, linear regression analyses will be performed. For the intervention group, additional to the claims data, there will be the data gathered within the study. To analyze their impact on the reduction of the HbA1c-parameter, these data will be included as fixed effects in a linear mixed model in the sub-group of intervention patients.

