##### Sample size calculation

###### General practitioner study

Sample size calculation refers to the primary endpoint and is based on a t-test (α = 0.05; power = 0.8). We assume that HbA1c in the intervention group will decrease on average by 0.2%-points (standard deviation (sd) of 2.3) compared to the control group. The estimator results from the assumption that at least 50% of T2DM-patients have a need for periodontitis therapy [15, 20] and that they’re able to lower their HbA1c by 0.6%-points through therapy [8]. Out of these patients, an assumed 66% will use the referral to a dentist [21]. To account for cluster effects (patients clustered in practices), an intra-class-correlation of 0.03 and a cluster size of 10 patients per practice is assumed. For the control group calculated from claims data, we assume that it contains at least double the number of patients than the intervention group (allocation in a 2:1 ratio for control vs. intervention group). This results in a sample size of 1980 intervention patients (198 practices, 10 patients each) and 3960 control patients. With an assumed drop-out rate of 20%, there will be 2480 intervention patients (248 practices, 10 patients each) and 4950 control patients. Sample size calculation was performed using PASS v16.0.3.

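### The fixed-effect list for the GP study's primary mixed model omits group, so the sentence as written contains no coefficient that tests the stated null hypothesis

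*Protocol article*

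**What the plan says.** All references are to the protocol article.

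- **Hypothesis** (Statistical hypotheses and analyses, General practitioner study). The two means compared "represent the reduction of the HbA1c-parameter between baseline (T0) and after 4 quarters (T1) in both groups", and the test is made "on a two-sided significance-level of 5" percent.
- **Primary model** (same section). This is a hierarchical linear mixed model. For the test of this hypothesis, "the dependent variable will be “reduction of HbA1c between T0 and T1". The contents are then given: "The model contains the practice as a random effect and HbA1c at baseline (T0), age, sex, insurance status, state and residential area", these last six entering as fixed effects. A restriction follows: "Here, only variables that are also included in claims data can be used".
- **Dentist study** (the matching paragraph under its own heading). "The model contains the practice as a random effect and the group (intervention vs. control), age, sex, insurance status, state and residential area".
- **The other GP mixed model**. Additional study data are to be related to HbA1c reduction, and "these data will be included as fixed effects in a linear mixed model in the sub-group of intervention patients".
- **Sample size** (General practitioner study). The calculation "is based on a t-test (α = 0.05; power = 0.8"), for a difference of 0.2 percentage points between the groups.

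**The concern.** The hypothesis is a comparison of two groups. A regression model tests it through a coefficient for group, and the GP list has none. The six listed fixed effects are baseline HbA1c and five demographic or administrative variables, and none of them identifies the arm.

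The practice random effect cannot do the job either. Intervention practices are removed from the control data by registration number, so every practice belongs wholly to one group. A group difference is then constant within practice, and a model without a group term treats it as ordinary variation between practices.

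What is at stake is whether the published description of the primary analysis can be carried out as a test of its own hypothesis. This matters somewhat more here than in a randomised comparison. The control group is built from claims and disease-management-program data, so the adjusted group coefficient is the estimate on which the GP conclusion rests.

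**Working it through.** **1. The two model sentences side by side**

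| Element | GP study | Dentist study |
|---|---|---|
| Hypothesis | equal mean HbA1c reduction in both groups | equal rate of new diabetes diagnoses in both groups |
| Random effect | practice | practice |
| Group as fixed effect | not listed | listed |
| Baseline value of the outcome | listed | not listed |
| Age, sex, insurance, state, residence | listed | listed |

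The sentences follow one template. In the GP version, baseline HbA1c stands where the dentist version has group. The only other GP mixed model that is named is confined to intervention patients and cannot give a between-group contrast. No other section of the article adds group to the GP primary model.

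**2. Is the study planned for a group contrast?**

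Inputs from the GP sample-size section: difference 0.2, SD 2.3, alpha 0.05 (two-sided in the hypothesis section), power 0.80, ICC 0.03, 10 patients per practice, control to intervention 2:1, drop-out 20%.

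- Intervention n before clustering: (1 + 1/2) × 2.3² × (1.960 + 0.842)² / 0.2² = 1.5 × 5.29 × 7.849 / 0.04 ≈ 1557.03, rounded up to 1558. Control: twice the unrounded figure, rounded up to 3115.
- Design effect: 1 + (10 − 1) × 0.03 = 1.27, applied to both groups.
- With clustering: 1558 × 1.27 = 1979 and 3115 × 1.27 = 3956. The article states 1980 and 3960, which agrees after rounding to whole practices and doubling.
- Drop-out: 1980 / 0.8 = 2475, which is 2480 in 248 whole practices; 3960 / 0.8 = 4950. Both match the article.

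The planned numbers are therefore those of a two-group comparison. At 1980 and 3960 patients the standard error of the group difference is 2.3 × √(1.27 × (1/1980 + 1/3960)) = 0.071, and power for 0.2 is 0.80.

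**3. Where does the difference go if group is left out?**

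One third of practices are intervention and two thirds control. A difference of 0.2 that is constant within practice adds (1/3) × (2/3) × 0.2² = 0.009 to the between-practice variance. The planning assumptions give that variance as 0.03 × 2.3² = 0.159, so it rises by about 6%, to about 0.168. This holds if the covariates are balanced between groups. If they are not, part of the difference moves into their coefficients. How much cannot be computed, because the article gives no covariate distributions.

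**4. Illustration**

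One simulated data set used the planning values (198 and 396 practices of 10, difference 0.2) with baseline HbA1c as the only covariate. Without group, the fit returned an intercept, a baseline slope and a practice variance. With group added, it also returned a coefficient of 0.219 (standard error 0.068, p = 0.001). This shows only which parameters each model contains. It is not evidence of bias or loss of power.

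**The case against.** The strongest reply is that the section, read as a whole, leaves no doubt about what will be compared. The hypothesis names both groups, the model is introduced expressly for testing it, and the sample size is that of a two-group test. On this view the list gives the adjustment covariates and group is taken for granted. The claims-data restriction fits, since group is defined by data source and is not a claims variable.

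Much of this stands. It shows that the comparison is intended and that the omission is most likely a slip. It does not make the sentence correct. The sentence states what the model contains, and the parallel dentist sentence names group explicitly, so a reader cannot tell that the GP list covers adjustment variables only. Nor is this a detail left to an analysis plan that is not shown: the article gives a specific list, and the list is incomplete.

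Several stronger readings are tempting, and the documents do not support them:

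- *That any group comparison would be post hoc.* Outcome, contrast, sidedness, alpha, covariates and random effect are all fixed. Adding the group main effect that the hypothesis calls for leaves little analytic freedom.
- *That the trial will produce no effect estimate.* This would follow only if the sentence were run literally and reported as it stood. Nothing in the article suggests that plan.
- *That the difference would show up only as between-practice variance.* Covariates that differ between recruited patients and claims-based controls could take up part of it.
- *That the faulty model is bound to be programmed twice.* The sentence on independent counter-programming stands under the dentist study, and its application to the GP model is an inference.

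**Conclusion.** The point holds as an error in the written specification. The GP primary model as listed has no coefficient for the intervention-versus-control contrast named in the null hypothesis and assumed in the sample size. Taken literally, a 0.2-point difference would appear as roughly a 6% increase in between-practice variance, less whatever unbalanced covariates absorb. That figure assumes the planning SD, ICC and 2:1 ratio, an equal number of patients per practice, and practices that belong wholly to one group.

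The conclusion is confined to the article's sentence. It does not say that the trial's actual analysis lacks a group term, because an analysis plan that is not shown may contain it. The design, hypothesis, alpha and sample size are unaffected. The omission is most likely a drafting slip, but it concerns the one term that carries the primary hypothesis and should be corrected before the GP comparison is run.

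**What to change.** In the General practitioner study paragraph of Statistical hypotheses and analyses:

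1. Add group, intervention versus control, to the fixed effects. Keep the six covariates already listed and practice as the random effect.
2. State that the null hypothesis is tested by the group coefficient, reported with its two-sided 95% confidence interval.
3. State that the limit to variables available in claims data applies to the adjustment covariates. Group is known from the data source and is not subject to it.

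The cost is two or three sentences. No data, patients or practices are added, and the sample size stands. If the analysis plan already has the group term, the change only brings the published text into line with it.
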